**Appendix H: Adverse event forms**

**H1: Adverse event reporting form**

| ADVERSE EVENT REPORTING FORM | | | | | | | CIRCLE AS APPROPRIATE:FSAT/ IRS/LLIN | | | | | | |
| --- | --- | --- | --- | --- | --- | --- | --- | --- | --- | --- | --- | --- | --- |
| **Person ID:**  ___________ | **Cell:** | | | | **Compound/house code:** | | | | **Date:**  \|___\|___\| / \|___\|___\| / \|___\|___\| | | | | |
|  | ***Complete on day first reported*** | | | | ***Complete on day first reported and update as needed*** | | | | | | | ***Complete on final day*** | |
| **Event** | **Date event onset (d)** | **Date event report (e)** | **Name person reporting** | **Max severity* (f)** | | **Max relationship† (g)** | | **Serious? ‡ *(Y/N)*(h)** | | **Episodic?**  ***(Y/N)*(i)** | **Outcome †† (j)** | | **Date event resolved‡‡ (k)** |
|  |  |  |  |  | |  | |  | |  |  | |  |
|  |  |  |  |  | |  | |  | |  |  | |  |
|  |  |  |  |  | |  | |  | |  |  | |  |
|  |  |  |  |  | |  | |  | |  |  | |  |
|  |  |  |  |  | |  | |  | |  |  | |  |

*** Severity:** Rank on scale of 1-4: mild = 1; moderate = 2; severe = 3, life-threatening = 4 **† Relationship:** Rank on scale of 0-4: none = 0; unlikely = 1; possible = 2; probable = 3; definite = 4

**‡ Serious:** Criteria for SAE: fatal, life-threatening, results in or prolongs hospitalization, results in significant or persistent disability or capacity requires medical / surgical intervention to prevent serious outcome.

If serious, report to core facility staff immediately.

**†† Outcome:** Rank on scale of 1-5: resolved without sequelae = 1; resolved with sequelae = 2; AE still present at study end/discontinuation, but improving = 3; subject died = 4; unknown = 5

**‡‡ Date event resolved:** Complete on Day 42 – If AE still ongoing at end of follow-up, indicate in question.

| SERIOUS adverse event form – initial report | | **Date of SAE Report:**  \|____\|____\|/\|____\|____\|/\|____\|____\|  *day month year* | | | |
| --- | --- | --- | --- | --- | --- |
| **Person ID:**  \|_____\|_____\|_____\|_____\|_____\|_____\|_____\| | | **Date enrolled:**  \|____\|____\|/\|____\|____\|/\|____\|____\|  *day month year* | | | |
| **Person name:** | | **Age:** \|_____\|_____\| years | | **Gender:**  Male Female | |
| **Parent name:** | |  | | | |
| **Event description**:__________________________________________________________________________________________________  *(symptom, sign, or laboratory abnormality)* | | | | | |
| **Indicate reason for serious AE**  *(tick all that apply):*  Death  Life-threatening  Resulted in or prolonged hospitalization  Required medical / surgical intervention to prevent serious outcome  Resulted in significant / persistent disability or incapacity Other:____________________ | **Date of event onset:**  \|____\|____\|/\|____\|____\|/\|____\|____\|  *day month year* | | | | **Maximum event severity:**  Mild  Moderate  Severe  Life-threatening |
|  | **Date of site awareness:**  \|____\|____\|/\|____\|____\|/\|____\|____\|  *day month year* | | | |  |
| **EVENT SUMMARY** *(include details of event, associated signs and symptoms, possible alternative etiologies, relevant past medical history, and medical management):*  *____________________________________________________________________________________________________________*  *____________________________________________________________________________________________________________*  *____________________________________________________________________________________________________________*  *____________________________________________________________________________________________________________*  *____________________________________________________________________________________________________________*  *____________________________________________________________________________________________________________* | | | | | |
| **Study product name:** Artemether-lumefantrine | | | **Route of study product:** Oral | | |
| **Dosing schedule at SAE onset:** | | | | | |
| **Date study product first started** *(Day 0)***:**  \|___\|___\|/\|___\|___\|/\|___\|___\|  *day month year* | | | **Date study product last taken prior to onset of SAE:**  \|___\|___\|/\|___\|___\|/\|___\|___\|  *day month year* | | |
| **Relationship to study product:**  None  Unlikely  Possible  Probable  Definite | | | **If not associated, is event related to:**  Study procedure  Other condition or illness  Other medication  Other____________________________ | | |

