During a second visit, one month after initial LLIN distribution the correct usage of LLINs will be evaluated: the correct hanging of LLINs will be confirmed and household members will be asked to explain how they use the net. If needed, instructions about correct use will be repeated and additional nets can be provided if nets are missing or found to be torn. A third visit will occur to re-assess the quality and use of the nets 6 months after the first visit, in conjunction with the second round of IRS. At this point new ownership and quality will be re-assessed and new nets will be distributed as needed. All information on net use and quality will be recorded (appendix D).

*Focal Screening and Treatment (FSAT)*

Screening of a sentinel population within households

The FSAT utilizes individuals aged 6 month to 20 years as a sentinel group to indicate malaria exposure in the household because this age-group experiences the highest parasite burden [23-24]. For this age group all individuals will be tested for parasites using RDTs regardless of presence of symptoms or not. However clinical care will not be restricted to just this age group. All age groups may experience clinical malaria in our setting ([name] *et al.*, in preparation) and therefore those individuals over 20 years who are found to have fever will also be tested by RDT and receive treatment as oart of the FSAT intervention.

The FSAT campaign will take place in intervention hotspots in March 2012; a second round of FSAT is planned to take place in September 2012. Both campaigns will follow identical procedures.

Screening the sentinel group

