Treatment will be carried out using artemether-lumefantrine (Coartem, AL) according to national guidelines. AL is an antimalarial drug with an excellent safety profile; limited data on safety are available for children under 6 months and pregnant women, both groups will therefore be excluded from AL treatment (see below) but receive clinical care when necessary. As detailed below, all those who are given Coartem will be actively followed-up to monitor any side effects. This monitoring will happen on all days of treatment and one week after the start of treatment. If given to parasite-free individuals, AL will provide an effective prophylactic effect for 3-4 weeks, which has been shown to be highly beneficial for malaria control purposes in high endemic regions [36]. In parasite carriers, AL effectively clears asexual parasites and gametocytes, the parasite stage responsible for transmission [35]; the timing of FSAT is chosen to ensure individuals are parasite and gametocyte-free before the start of the peak transmission season. For those receiving AL, the first dose will be supervised and then instructions will be provided for taking of the second dose which will be issued. Teams will return to compounds the next day to administer and supervise the third dose and distribute the fourth. They will return again on the third treatment day to again administer and supervise the fifth dose and distribute the sixth. At the same time any side effects will be noted. (see appendix G & H).

All participants will be told their haemoglobin level immediately, and any person found to be anaemic will be provided haematinics according to national guidelines.

Treatment of risk groups: children <6 months and pregnant women

Children below 6 months of age will be excluded from the study; they will be screened for fever and referred to a health facility where needed but will not be included in FSAT.

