c. Risks to intervention participants

None of the interventions that are proposed in this study are experimental. LLINs and IRS are part of the malaria control efforts by the DOMC for the district; larviciding has been done in districts bordering or close to Rachuonyo district, in Nyando, Kisii, Suba and Kakamega districts [22]. All insecticides used will have been approved by DOMC and PCPB prior to application. The FSAT approach to screen asymptomatic children and treat all inhabitants of households where ≥1 individual is found parasite positive by RDT has not been done routinely in Kenya but is an extension of screening and treatment of asymptomatic individuals that is proposed under the Kenyan National Malaria Strategy for 2009-2017[[13](#_ENREF_13)]. The national strategy does not currently propose to treat household members of asymptomatic parasite carriers; the approach is justified by evidence of clustering of parasite carriage at household level [2, 6, 25, 33] and the low sensitivity of RDTs for detecting all epidemiologically relevant parasite densities [[14](#_ENREF_14)]. We will provide supervised treatment with the first line antimalarial drug AL that has an excellent safety profile and is recommended for treatment of symptomatic and asymptomatic malaria infections in Kenya [[13](#_ENREF_13)]. We will also closely monitor and document any reported side effects of all interventions by questionnaires on all days of treatment and one week after treatment, IRS and ITN distribution.

d. Benefits to survey participants

All participants of the cross-sectional survey will benefit from knowing their haemoglobin level and whether they have a clinical malaria infection. Any participant with low haemoglobin will receive treatment for anaemia. All individuals who are diagnosed with a clinical malaria episode will be treated with AL according to Kenya national guidelines.

e. Risks to survey participants

This survey is of minimal risk to participants. Blood will be collected by fingerprick only using a sterile lancet, and the total amount of blood collected is very small (200-300μl); participants may experience only a small bruise at the site where we collect the blood. Blood draws will be carried out by trained medical or laboratory staff members to ensure these are done in as safe a manner as possible.

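### Form H1 closes adverse events on Day 42, a day no described visit supplies and that is anchored only for AL, and its outcome list has no code for an event that is ongoing and not improving (minor)

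*Protocol*

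**What the plan says.** **The form.** H1 in Appendix H is used for every intervention with person-level reporting; its header reads "CIRCLE AS APPROPRIATE:FSAT/ IRS/LLIN". Outcome and resolution date appear to sit together under a block to be completed on the final day, although the column alignment in the extracted table is not certain. The footnote to the resolution date reads "Complete on Day 42 – If AE still ongoing at end of follow-up", and goes on to tell staff to indicate such an event in that item. The outcome codes are "resolved without sequelae = 1; resolved with sequelae = 2", followed by "AE still present at study end/discontinuation, but improving = 3; subject died = 4; unknown = 5".

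**The contacts.** For AL, section 9f states: "This monitoring will happen on all days of treatment and one week after the start of treatment". Section 12c says that side effects of all interventions are documented "by questionnaires on all days of treatment and one week after treatment, IRS and ITN distribution". For spraying, section 9f has households revisited about one week later. A later visit is planned for nets: "During a second visit, one month after initial LLIN distribution the correct usage of LLINs will be evaluated". Another follows at six months. Both are described in terms of net presence, condition and use.

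**The reference day.** Day 0 appears only on the serious adverse event initial report, as the date the study product was first started, and that form is pre-printed for AL.

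**The concern.** Anyone completing H1 as written meets two problems.

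First, the form calls for an entry on a day when no described contact takes place. For an event attributed to spraying or nets, the day itself cannot be worked out from the documents.

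Second, if the event is known to be present and is the same or worse, none of the five outcome codes is true. Code 3 asserts an improvement that was not seen. Code 5 discards what is known.

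What is at stake is the quality of the safety record. Section 9f gives AL to everyone treatable in a house with a positive test, and accepts that some of them will carry no detectable parasites. Section 12c supports this partly with a commitment to monitor closely and document side effects of all interventions. The close-out form should be able to deliver that.

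**Working it through.** The plan gives no figure to reproduce. The check sets the form against the visit schedule, then the outcome codes against the states an event can be in.

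**1. Is there a contact at Day 42?**

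- AL, section 9f: last contact 7 days after the start of treatment, so Day 7. Gap to Day 42: 42 − 7 = 35 days; 35/42 = 83%.
- AL, section 12c, reading the week as running from the end of treatment: section 9f gives six doses over three days (Days 0 to 2), so the last contact is about Day 2 + 7 = Day 9. Gap: 42 − 9 = 33 days; 33/42 = 79%.
- Spraying and nets: about one week after each, so 35 days again if the day of spraying or distribution is taken as Day 0. That is an assumption, because the protocol does not define it.
- One-month net visit: about Day 30 from distribution. It is not Day 42 and is not described as a safety contact.
- Six-month net visit: well after Day 42, again about nets.
- Section 11 activity table: no safety contact is listed.
- Cross-sectional surveys: these sample randomly selected compounds, and the Appendix E questionnaire has no adverse event item.

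No described visit therefore supplies the Day 42 assessment. Sections 9f and 12c also differ by about two days on where the AL week starts.

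**2. Can Day 42 be located for each intervention?** For AL, yes, from the first intake. For spraying and nets, no: Appendix F sends their events to the adverse event forms, and no Day 0 is given for them.

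**3. Do the H1 outcome codes cover the possible states?**

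- Resolved: two codes (1, 2).
- Died: one code (4).
- Still present and improving: one code (3).
- State not known: one code (5).
- Still present and unchanged or worse: no code.

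**4. Does another field or form fill the gap?**

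- The H1 date column: in part. The footnote tells staff to indicate an event still ongoing. That records persistence, not direction.
- H3: yes, for serious events. It has an option for an ongoing event, with a follow-up report to come later.
- H1 maximum severity: in part. It appears to fall under the columns that may be updated, so a worsening that raises the grade could show there. An unchanged event would not.

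What remains is the H1 outcome column for non-serious events that persist without improving.

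**The case against.** The strongest reply is that this is a loose end on a form and not a failure of safety follow-up. Several parts of that reply stand.

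- A reader might infer that every unresolved event ends on record as improving or unknown. The documents do not support that: the date column flags an ongoing event and H3 covers serious ones. The gap is confined to one column.
- A reader might infer that known events are dropped after one week. No section says so. The one-week contacts are for eliciting side effects, a Clinical Officer is available to advise on them, and serious events are to be reported at once. A short elicitation window and a later close-out could coexist; what is missing is a description of how the later entry is obtained.
- A reader might infer that the safety summary is biased towards benign outcomes. The protocol lists no safety outcome and describes no safety summary in its analysis section, and an unknown code is not a benign one.
- A reader might set the 3 to 4 weeks that section 9f gives for AL against the one-week contact. That figure is a prophylactic duration, not a period of adverse event risk.
- The difference between sections 9f and 12c is about two days of wording and would not merit a comment alone.

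None of this supplies a Day 42 contact, a reference day for spraying and nets, or a true outcome code for an event that persists unimproved. That H3 has an ongoing option shows the category was recognised for serious events.

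**Conclusion.** The point holds as a minor error in the safety form. H1 sets a close-out day that no described contact serves, the day is undefined for two of the three interventions the form covers, and the outcome list lacks one state.

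The distance is 35 days from the section 9f wording, or 33 from section 12c on the reading that the week follows the last treatment day. These figures, and the matching 83% and 79%, measure calendar time without a visit. They do not estimate how many events would be missed or miscoded, and the documents give nothing from which to estimate that.

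The conclusion rests on two assumptions: that the contacts described are all that is planned, and that the footnote on the date column does not also supply an outcome code.

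**What to change.** 1. Add an H1 outcome code for *ongoing, unchanged or worse*.
2. Reconcile sections 9f and 12c with H1, so that the close-out day on the form is a contact that takes place and the AL week has one stated starting point.
3. Define the reference day separately for AL, spraying and nets.
4. Where feasible, update events still open at one week at the one-month net visit, and state that H1 is completed there for those events. In March 2012 this visit is to the same hotspot compounds, since section 11 rolls out nets and FSAT together, with spraying straight after. No one-month net visit is described after the later rounds, so the protocol should say which contact closes open events then.

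The cost is a form edit, a sentence or two in sections 9f and 12c, and one added question at an existing visit. Any return visit in later rounds could be limited to people with an open event.

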**H12: Serious adverse event form–initial report**

**H3: Serious adverse event form – management and outcome report**

| SERIOUS ADVERSE EVENT FORM – MANAGEMENT REPORT | |
| --- | --- |
| **Date of SAE Report:**  \|____\|____\|/\|____\|____\|/\|____\|____\|  *day month year* | **Study**  **Number:** \|_____\|_____\|_____\|_____\|_____\| |

| **Study product status:** *(tick all that apply)*  No change in dose  Study treatment held  Study treatment discontinued permanently  Other____________________________________ | | | | **Patient management:** *(tick all that apply)*  Patient hospitalized  Blood transfusion given  Intravenous fluids given  Parenteral quinine given  Other____________________________________  Other____________________________________  Other____________________________________ | | | | | | |
| --- | --- | --- | --- | --- | --- | --- | --- | --- | --- | --- |
| **CONCOMITANT MEDICATIONS** *(List relevant concomitant medications the subject was taking up to 1 month prior to SAE onset.)* | | | | | | | | | | |
| **Medication** | **Start date**  *(dd/mm/yy)* | **Stop date**  *(dd/mm/yy)* | | | **Total daily dose** | | **Indication** | | **Suspect**  **for SAE** | |
|  | \|___\|___\|/\|___\|___\|/\|___\|___\| | \|___\|___\|/\|___\|___\|/\|___\|___\| | | |  | |  | | □ Yes  □ No | |
|  | \|___\|___\|/\|___\|___\|/\|___\|___\| | \|___\|___\|/\|___\|___\|/\|___\|___\| | | |  | |  | | □ Yes  □ No | |
|  | \|___\|___\|/\|___\|___\|/\|___\|___\| | \|___\|___\|/\|___\|___\|/\|___\|___\| | | |  | |  | | □ Yes  □ No | |
|  | \|___\|___\|/\|___\|___\|/\|___\|___\| | \|___\|___\|/\|___\|___\|/\|___\|___\| | | |  | |  | | □ Yes  □ No | |
| **RELEVANT LABORATORY TESTS** | | | | | | | | | | |
| **Test** | **Collection date**  *(dd/mm/yy)* | **Result** | **Site normal range** | | | **Most recent value prior to SAE** | | **Collection date**  *(dd/mm/yy)* | | |
|  | \|___\|___\|/\|___\|___\|/\|___\|___\| |  |  | | |  | | \|___\|___\|/\|___\|___\|/\|___\|___\| | | |
|  | \|___\|___\|/\|___\|___\|/\|___\|___\| |  |  | | |  | | \|___\|___\|/\|___\|___\|/\|___\|___\| | | |
|  | \|___\|___\|/\|___\|___\|/\|___\|___\| |  |  | | |  | | \|___\|___\|/\|___\|___\|/\|___\|___\| | | |
|  | \|___\|___\|/\|___\|___\|/\|___\|___\| |  |  | | |  | | \|___\|___\|/\|___\|___\|/\|___\|___\| | | |
| **RELEVANT DIAGNOSTIC TESTS** | | | | | | | | | | |
| **Test** | **Collection date**  *(dd/mm/yy)* | **Results/Comments** | | | | | | | | |
|  | \|___\|___\|/\|___\|___\|/\|___\|___\| |  | | | | | | | | |
|  | \|___\|___\|/\|___\|___\|/\|___\|___\| |  | | | | | | | | |
|  | \|___\|___\|/\|___\|___\|/\|___\|___\| |  | | | | | | | | |
| **Outcome of event:**  Ongoing: [SAE Follow Up Report to be completed and sent at later date]  Resolved without sequelae  Resolved with sequelae _____________________________  Death | | | | | | **If resolved or died, indicate date:**  \|___\|___\|/\|___\|___\|/\|___\|___\|  *day month year* | | | | |
| **Completed by:**  **Name printed: ____________________________ Signature:** ___________________________ **Date:** \|___\|___\|/\|___\|___\|/\|___\|___\|  *day month year*  **Investigator’s**  **Name printed: ____________________________ Signature:** ___________________________ **Date:** \|___\|___\|/\|___\|___\|/\|___\|___\|  *day month year* | | | | | | | | | |  |

# H4: Guidelines for Grading Patient Symptoms, signs and laboratory findings

## Table A. Guidelines for grading patient symptoms

|  | **Grade 1**  **MILD** | **Grade 2**  **MODERATE** | **Grade 3**  **SEVERE** | **Grade 4**  **LIFE THREATENING** |
| --- | --- | --- | --- | --- |
| **Subjective fever in the past 24 h** | N/A | Present (Yes) | N/A | N/A |
| ***Weakness*** | Mild decrease in activity; For children – weak, but still playing | Moderate decrease in activity; For children – weak, and playing limited | Not participating in usual activities; For children – not playing | Prostration |
| **Muscle and/or joint aches*** | Mild and/or localized complaints | Diffuse complaints | Objective weakness; function limited | N/A |
| **Headache*** | Mild, no treatment required | Transient, moderate; treatment required | Severe, constant; requires narcotic therapy | Intractable; requires repeated narcotic therapy |
| **Anorexia** | Decreased appetite, but still taking solid food | Decreased appetite, avoiding solid food but taking liquids | Appetite very decreased; Refusing to breast feed, no solids or liquids taken (< 2 years < 12 hr; > 2 years < 24 hr) | Appetite very decreased; Refusing to breast feed, no solids or liquids taken (< 2 years > 12 hr; > 2 years > 24 hr) |
| **Nausea*** | Mild, transient feeling of impending vomiting; maintains reasonable intake | Moderate and/or constant feeling of impending vomiting; intake decreased | Severe, constant feeling of impending emesis; intake decreased significantly | N/A |
| **Vomiting** | 1 episode per day | 2-3 episodes per day | Orthostatic hypotension or IV fluids required | Hypotensive shock or hospitalisation required for IV fluid therapy |
| **Abdominal pain*** | Mild (1-3 on a scale of 1 to 10) | Moderate (4-6 on a scale of 1 to 10) | Moderate to severe (> 7 on a scale of 1 to 10) | Severe – hospitalilsation for treatment |
| **Diarrhea** | Transient 3-4 loose stools/day | 5-7 loose stools/day | Orthostatic hypotension or > 7 loose stools/day or IV fluids required | Hypotensive shock or hospitalilsation for IV fluid therapy required |
| **Cough** | Transient / intermittent | Persistent / constant | Uncontrolled | Cyanosis, stridor, severe shortness of breath |
| **Pruritis** | Transient pruritis | Pruritis that disturbs sleep | Severe, constant pruritis, sleep disturbed | N/A |
| **Tinnitus*** | Mild, transient ringing or roaring sound | Moderate, persistent ringing or roaring sound | Severe ringing or roaring sound with associated hearing loss | N/A |
| **Behavioural changes** | Mild difficulty concentrating; mild confusion or agitation; activities of daily living unaffected; no treatment | Moderate confusion or agitation; some limitation of activities of daily living; minimal treatment | Severe confusion or agitation; Needs assistance for activities of daily living; therapy required | Toxic psychosis; hospitalilsation required |
| **“Flu”**  **(viral URI)** | Mild nasal congestion, mild rhinorrhea | Moderate nasal congestion, moderate rhinorrhea | N/A | N/A |
| **Allergic reaction** | N/A | N/A | Urticaria | Severe urticaria  anaphylaxis, angioedema |
| **Convulsion** | N/A | N/A | Localized or generalized seizure | Status epilepticus |
| *** Assess only in children > 3 years of age. Answer N/A for younger children and those unable to answer.** | | | | |

Reference – Based on WHO Toxicity Grading Scale for Determining the Severity of Adverse Events
